#### 2.2.3. Data Collection and Outcomes

As described, all home cooks who access the videos will be invited to answer a brief post-video survey about acceptability and satisfaction. At the end of each video, viewers will have the opportunity to “opt-in” to complete a short survey to assess satisfaction, engagement, and comprehension. If they agree, they will be redirected to a study information sheet and screening questionnaire. If they fit the study’s inclusion criteria, they will proceed to a brief survey via Qualtrics that will assess satisfaction, engagement, and comprehension of the video content. The brief survey will take less than 2 min to complete.

### 2.3. Population Intervention 2

#### 2.3.1. Overview

The second type of evaluation in the population-based setting will use a single arm, quasi-experimental pre- and multiple post-test study design. A sample (*n* = 500) of participants will be recruited to participate in a ~10 min survey to evaluate three specific videos across process (feasibility, satisfaction, engagement, comprehension) and preliminary outcome (motivation, opportunity, ability) metrics. The participants will be recontacted again at 3 and 6 months to complete follow-up surveys about longer-term outcomes.

#### 2.3.2. Study Population and Recruitment

The inclusion and exclusion criteria are the same for both population-level interventions. Potential participants should be 18 years or older, responsible for at least half of their household food preparation, prepare meals at home at least twice each week, have access to the internet, and understand English. The following groups will be excluded: adults unable to consent, individuals who are not yet adults (infants, children, and teenagers), and prisoners.

We will recruit participants for this evaluation by utilizing ResearchMatch and Build Clinical. ResearchMatch is a website that connects potential participants with researchers by emailing individuals with a recruitment message that explains the basic details of the research study. If individuals are interested in participating in the study, they will be directed to a screening questionnaire. Build Clinical will run an online advertisement campaign on online and social media websites, such as Facebook, Instagram, and X (formerly Twitter). When individuals press on these digital advertisements, they will be redirected to a landing page where they can learn more about the study and fill out a screening questionnaire.

If the interested individual from either platform is eligible for the study, a research assistant will call the individual and further explain the goals and procedures of the intervention. After this phone call, the research assistant will send the individual an email with a link to the information sheet for exempt research. Proceeding to the survey will serve as a proxy for written consent. Participants will be offered a USD 10 incentive for completion of the pre- and post-video surveys, and an additional USD 5 incentive for completion of each follow-up assessment (3 and 6 months; USD 10 for completion of both; USD 20 for completion of the entire study).

A sample size of 500 is sufficient to provide 95% power to detect an effect size of 0.43. Participants will be purposively sampled by age, race/ethnicity, gender, and income to optimize the diversity of our sample. Our goal is for our sample to mirror the US census demographic composition of the most recent census (Gender—Male: 49.6%, Female: 50.4%, Non-binary: natural fallout; Race—White: 76%, Black/AA: 14%, Asian or Pacific Islander: 6%, American Indian/Alaskan Native/Other: 2%; Hispanic Ethnicity—Hispanic: 19%, Non-Hispanic: 59%).

#### 2.3.3. Data Collection and Outcomes

A structured survey (~10-min pre-post survey) will evaluate specific educational videos across process (feasibility, usage, acceptability, and satisfaction) and preliminary outcome (motivation, opportunity, and ability) metrics. The enrolled participants will also complete 3- and 6-month follow-up surveys. The structured survey will ask about demographic characteristics and will obtain baseline information about motivation, opportunity, and ability as they relate to food-waste prevention. The survey will also contain three embedded food-waste prevention videos for the participants to view. After viewing each video, the participants will be asked to answer questions about the content to assess video satisfaction, engagement, recall, and comprehension of information, in addition to questions about motivation, opportunity, and ability. The 3- and 6-month follow-up surveys will primarily focus on motivation, opportunity, and ability to reduce household food waste.

#### 2.3.4. Data Analyses for Population Interventions 1 and 2

Descriptive characteristics of our study sample will be calculated as means ± standard deviations, frequencies, chi-square contingency analyses, and standardized residuals, unless otherwise noted. Changes in motivation, opportunity, and ability will be analyzed as continuous or categorical variables. Mixed factorial analyses of covariance (ANCOVA) with repeated measures will be used to determine whether mean differences exist in participant satisfaction, engagement, and comprehension after controlling for the influence of socio-demographic- (age, race and ethnicity, marital status, education, and income) and household-related characteristics measured at baseline. Differences will be estimated for all categorical variables using McNemar’s exact significance probability testing for paired nominal data. All quantitative statistical analyses will be accomplished using IBM SPSS Statistics.

### 2.4. Community Intervention

#### 2.4.1. Overview

All eight modules of the CHEF-WPM intervention will be presented in sequence over an eight-week period, facilitated by a chef–instructor with assistance from culinary students. The course will include synchronous discussions and group viewing of the CHEF-WPM video series hosted on Kajabi. Evaluation of the remote community-based intervention will use a mixed methods evaluation study design. The objectives of this mixed methods evaluation are to assess (1) intervention implementation (fidelity), satisfaction, engagement, and comprehension; (2) intervention outcomes (motivation, opportunity, ability, and household food waste); and (3) exploratory outcome (sustainable dietary behaviors). A maximum of 60 participants will be recruited in partnership with local community organizations for quantitative data-collection activities. Quantitative data collection will occur pre- and post-8-week intervention and at 6 months follow-up. A purposive sample of 20 participants will be recruited to participate in in-depth interviews at 8 weeks post-intervention. Food waste will be measured via self-report methods among the participants (*n* = 60) at pre- and post-intervention and 6-month follow-up.

#### 2.4.2. Study Population and Recruitment

Potential participants will be 18 years or older, responsible for at least half of their household food preparation, prepare meals at home at least twice each week, have access to the internet, and understand English. The following groups will be excluded: adults unable to consent, individuals who are not yet adults (infants, children, and teenagers), and prisoners. Individuals who express interest in participating in the 8-week CHEF-WMP program will be screened for eligibility via telephone or a brief Qualtrics survey.

A convenience sample of 60 participants will be recruited for the community-level intervention, drawn primarily from a lower-income population in Philadelphia (3 cohorts of 20 individuals per cohort). This population includes a higher percentage of Black, Indigenous, and people of color than the US population. For the qualitative evaluation (in-depth interviews), a purposive sample (*n* = 20) of intervention participants will be recruited. Purposive sampling helps ensure sample diversity across age, income, educational attainment, household size, and baseline pre-disposition for food waste prevention. Participants will be recruited through university networks and in partnership with community organizations. Participants will be recruited via phone calls and/or email, digital and paper advertisements, and QR codes. These organizations together generally attract participants reflecting the city’s diverse urban demographics, namely 44% Black, 13% Latino, 7% Asian; 46,000 median household income; and 20% poverty rate.

QR codes and email links will direct individuals to a Qualtrics screening questionnaire. If they qualify, they will proceed to a study information sheet that describes participation in detail. If they are still interested after learning more about participation, they will be asked to submit their contact information and a research assistant will contact them with further details about participation. Participants will be compensated a total of USD 150 for completing the evaluation activities (quantitative measures) and an additional USD 40 for completing an interview.

#### 2.4.3. Data Collection and Outcomes

The participants will complete a pre-intervention survey and measure their household food waste before beginning the 8-week intervention. At the completion of the intervention, participants will complete a post-intervention survey and again measure their household food waste. A purposive sample of participants, six from each cohort, will be recruited to complete in-depth interviews at the end of the intervention. We will follow up with all the participants 6-months after the intervention, where they will complete a 6-month post-intervention survey and measure their household food waste. These measures are described below.

For the *pre- and post-intervention surveys*, after viewing the study information page for exempt research, the participants will proceed to a structured survey that will ask about demographic characteristics and will obtain baseline information about motivation, opportunity, and ability as they relate to food-waste prevention. To the extent possible, the evaluation questions were replicated from existing surveys and tailored to this intervention, including the specific content of each media asset. After completing the pre-intervention survey, the participants will be provided a scale and food-waste diary and given a brief training by a study researcher on measuring their home food waste. They will keep a one-week food-waste diary, as described below. The participants will be asked to complete a brief satisfaction survey after each program session.

The post-intervention assessment will occur at the end of the 8-week program. A survey that includes the baseline *survey* questions and additional post-intervention questions will be sent to participants during the one-week period after their last intervention session. In this post-intervention survey, the questions will assess program satisfaction, engagement, recall, and comprehension of information, participants’ level of implementation of steps recommended in the videos, further engagement with and shares of videos, reactions to the intervention, and intention to continue engaging in food-waste prevention activities. Participants will again receive instructions on how to measure their food waste for one week. The 6-month follow-up assessment will include a similar survey and food-waste measurement.

For *household food waste*, the participants will measure their household food waste for one week via self-report before and after participating in the remote community-based class. The participants will be given a Taylor compact digital scale and trained on how to measure their food waste. Our team will create a training video and instructions for how to measure food waste at home and will provide visual reminders for key aspects of the measurement, such as what to classify as “avoidable” vs. “unavoidable”. The participants will be given a diary form and instructed that, before they or a household member discards any household food waste to any destination including the sink and whether it is trim from meat or produce, plate waste, prepared leftovers, spoiled food, etc., they should weigh the food, describe what it is (fruit, vegetable, cooked grain, etc.), and indicate its type (trim from cooking, spoiled food, leftovers, plate waste, or other), as well as their impression of whether the food waste was unavoidable (example, fish innards) or avoidable (example, spoiled milk from overbuying) through a simple coding system, taking a minute or less. This requires discussion and buy-in from household members. The participants will again be asked to participate in the food-waste assessment at the 6-month follow-up.

For *sustainable dietary practices*, at pre- and post-intervention, and the 6-month follow-up, the participants will be asked to complete a brief dietary assessment to measure the overall sustainability of their dietary practices. This assessment will be conducted using Diet ID via their metric called Dietary Impacts on Environmental Measures (DIEM). The DIEM metric helps us understand the environmental footprint of participants’ diets. Diet ID is a novel pattern-recognition-based method that facilitates fast, user-friendly, and scalable dietary assessment [20]. Participants will be prompted with two photos of diets and asked which of the two is more like what they usually eat. Once they have chosen, the participants will be prompted with another two photos and asked the same questions. Participants will answer questions about their gender, height, weight, age, dietary restrictions/allergies, and general physical activity level (low, moderate, high) before completing the dietary assessment. No identifiable information will be collected by Diet ID.

For *qualitative data collection*, a purposive sample (*n* = 20) of intervention participants will be recruited to maximize diversity across age, income, educational attainment, household size, and baseline pre-disposition for food-waste prevention. They will participate in in-depth interviews after intervention completion to evoke priorities, values, and wisdom related to food-waste prevention; reactions to the intervention; and effects on motivations, opportunities, and abilities, as well as barriers and facilitators for continued engagement in food-waste prevention behaviors, and potential co-benefits for other outcomes as well as undesired tradeoffs and spillovers. Interviews will be led by an experienced qualitative researcher, will be conducted on HIPPA-compliant Zoom, will last approximately 30–45 min, and will be audio-recorded and transcribed verbatim.

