### 2.1. Intervention

The overall goal of the CHEF-WPM intervention is to increase consumers’ motivation, perceived opportunity, and ability to reduce food waste using home-based culinary techniques. The intervention will include eight modules, each containing three to five brief (4–8 min) videos, as well as downloadable recipes and worksheets. CHEF-WPM is designed to be used *a la carte* or as a self-paced online course.

The eight module topics include:My whole plate: Meal Planning & Kitchen Management with a ‘No Food Waste’ Lens;Veggies: Roots to Stem;Fruit: Fresh or Bruised;Meat- & Plant-Based Proteins;Fish & Seafood: Sear It, Don’t Fear It;Bread, Grains, Snacks, Sweets;Cooking Liquids & Dairy;Leftovers Are My Jam.

Each module focuses on improving the *motivation*, *opportunity*, and *ability* to reduce food waste using home-based culinary techniques. The modules will highlight *motivations*, including saving money, avoiding waste, confidence, setting an example for children, and improving nutrition, pleasure, and environmental benefits. The modules will also focus on perceived *opportunity* and illustrate ways to shift contextual factors, such as time and schedule, kitchen arrangement and food storage, and technologies, among other aspects. *Ability* will be addressed via sharing techniques, recipes, and tricks to prevent and minimize food waste at home and problem-solving strategies for challenges to food waste prevention. Adapted from the work of ölander and ThØgersen [11], Figure 2 displays the conceptual framework guiding the CHEF-WPM program.

The content will be developed and filmed at Drexel’s College of Nursing and Health Professions’ Food and Hospitality Management Space, and in the kitchen studio of the food-waste educator. The developed content will be hosted on a freely accessible website, Kajabi (http://kajabi.com; accessed on 1 July 2024). The CHEF-WPM program will be built and delivered to key audiences as an online course on Kajabi. Kajabi is an “all-in-one” platform that we will use to build our program, engage with learners (participants), and collect feasibility and preliminary efficacy metrics. The videos will also be disseminated via social media (i.e., X [FKA Twitter], Instagram, TikTok) and through partnerships with food-security organizations, retailers, nutrition education programs, and others.

### 2.2. Population Intervention 1

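### The diary's avoidable/unavoidable code is the participant's impression, which the course may shift either way, so pre-post change in that split is not change in avoidable waste; total weighed discards are unaffected

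*Protocol article*

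**What the plan says.** Section 2.4.3 has participants "measure their household food waste for one week via self-report before and after participating in the remote community-based class", and repeat this at the 6-month follow-up. For each discard "they should weigh the food, describe what it is (fruit, vegetable, cooked grain, etc.), and indicate its type" (trim, spoiled food, leftovers, plate waste or other), and they add "as well as their impression of whether the food waste was unavoidable (example, fish innards) or avoidable (example, spoiled milk from overbuying". Training, a training video and instructions are planned; the team also "will provide visual reminders for key aspects of the measurement, such as what to classify as “avoidable” vs. “unavoidable". Instructions are given again at the post-course wave. The article describes no fixed item list and no recoding by the study team.

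Section 2.1 says the course is meant to "increase consumers’ motivation, perceived opportunity, and ability to reduce food waste using home-based culinary techniques". Its modules include "Veggies: Roots to Stem;Fruit: Fresh or Bruised", and its ability content consists of "sharing techniques, recipes, and tricks to prevent and minimize food waste at home".

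Section 2.4.2 describes a single group: "A convenience sample of 60 participants will be recruited for the community-level intervention". Household food waste is listed as an intervention outcome in section 2.4.1. The analysis in section 2.4.4 refers to change in discards and to food-waste variables in the plural. Avoidable waste is not named as an endpoint.

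**The concern.** A before-after comparison needs the same yardstick at each wave. Here one part of the measurement, the avoidable/unavoidable code, is a personal judgement, and the course teaches content that bears on it. Someone who regards vegetable tops as unavoidable waste at baseline may, once taught to cook them, call the same tops avoidable. A participant who wants to look successful may shift the other way. With no comparison group, neither shift can be separated from a real change in what is thrown away using the impression code alone.

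At stake is any statement about change in avoidable waste. Section 2.4.4 leaves room for one, because it does not say which food-waste variables will be analysed or that total weight leads. The results are meant to inform a later randomised trial (section 5.3) and policy and funding (Final Considerations).

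**Working it through.** The plan gives no effect size, variability or expected avoidable share for food waste, so there is no figure to reproduce. The arithmetic below is illustrative and every input is assumed.

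**Inputs (assumed)**
- A: avoidable share of baseline waste by weight, 0.4, 0.6 or 0.8. The unavoidable share is U = 1 − A and is taken as truly unchanged.
- d: real fall in avoidable waste, 0 or 20%.
- r: share of weight in the source category that is relabelled after the course, 10%, 20% or 30%.

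**Formulas**
- Unavoidable relabelled avoidable: recorded change = [A(1 − d) + U·r]/A − 1.
- Avoidable relabelled unavoidable: recorded change = (1 − d)(1 − r) − 1.
- Total weight: change = A(1 − d) + U − 1 = −A·d. It contains no r.

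Example with A = 0.6, d = 0.2, r = 0.1. First direction: (0.48 + 0.04)/0.6 − 1 = −13.3%. Second direction: 0.8 × 0.9 − 1 = −28%. Total: −0.6 × 0.2 = −12%.

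**Recorded change in avoidable waste when the real change is −20%** (r = 10% / 20% / 30%)

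| A | Unavoidable → avoidable | Avoidable → unavoidable | Total weight |
|---|---|---|---|
| 0.4 | −5.0% / +10.0% / +25.0% | −28% / −36% / −44% | −8% |
| 0.6 | −13.3% / −6.7% / 0.0% | −28% / −36% / −44% | −12% |
| 0.8 | −17.5% / −15.0% / −12.5% | −28% / −36% / −44% | −16% |

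**Recorded change when nothing really changes** (r = 10% / 20% / 30%)

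| A | Unavoidable → avoidable | Avoidable → unavoidable | Total weight |
|---|---|---|---|
| 0.4 | +15.0% / +30.0% / +45.0% | −10% / −20% / −30% | 0% |
| 0.6 | +6.7% / +13.3% / +20.0% | −10% / −20% / −30% | 0% |
| 0.8 | +2.5% / +5.0% / +7.5% | −10% / −20% / −30% | 0% |

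**Relabelling that exactly hides a real 20% fall:** set A(1 − d) + U·r = A, so r = A·d/U.
- A = 0.4: 0.08/0.6 = 0.13.
- A = 0.6: 0.12/0.4 = 0.30.
- A = 0.8: 0.16/0.2 = 0.80.

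**Variation:** suppose all waste, unavoidable included, really falls 15%. The break-even share of the remaining unavoidable weight is then 0.15A/(0.85U). For A = 0.6 this is 0.09/0.34 = 26%; for A = 0.8 it is 0.12/0.17 = 71%.

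A rule that depends only on food description and waste type sets r to zero for the impression code. Recorded change then equals change under that rule's definition, whatever participants come to think.

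**The case against.** The best reply is that the stated outcome is not the quantity at risk. Sections 2.4.1 and 2.4.4 and Table 1 speak of household food waste, discards and food-waste variables. Total weighed discards is a natural reading, and it is immune to relabelling. This stands. A reader might infer that the food-waste outcome as a whole is compromised; the documents do not support that.

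Second, the shift is inferred. Section 2.1 aims at motivation, perceived opportunity and ability and says nothing about diary classification. The training, reminders and repeated instructions may hold definitions constant, and their content is not shown. This stands in part: they may reduce drift, but the recorded item is still an impression. The two examples given, fish innards and milk spoiled through overbuying, are clear cases, whereas trim and bruised produce lie between them.

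Third, a reader might infer that relabelling will hide or reverse a true benefit. The direction cannot be settled from the documents. Reversal also needs substantial one-way relabelling, more than 30% of unavoidable weight at A = 0.6 and more than 80% at A = 0.8 for a real 20% fall, although only 13% at A = 0.4.

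Fourth, a reader might infer that the damage is irreversible. It is not: weight, description and type are recorded, so recoding remains possible, and how a derived variable is built is commonly left to an analysis plan.

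Last, a lookup is imperfect. Edible tops and inedible peel can share the vegetable-by-trim cell, the cause of waste (such as overbuying) is not recoverable, and type is itself self-coded, so a cut-away bruise could be trim or spoiled. This stands, and limits what the recoded split can claim.

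**Conclusion.** The point holds for the impression-coded split only. The protocol fixes that code as a participant judgement at each wave, places relevant teaching between waves, and follows one group without a comparator. Change in the split therefore cannot be read as change in avoidable waste. That the judgement shifts, and which way, is inferred from the course content and from ordinary reporting behaviour; the documents do not state it.

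Under the assumed inputs, a real 20% fall could be recorded as anything from −44% to +25%, while total weight moves only with the real change. That range shows sensitivity to assumptions and does not estimate the bias. Because total weight is unaffected, avoidable waste is not a named endpoint and the remedy uses data already planned, this is a cheap improvement, not a fault in the outcome as worded.

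**What to change.** - State in section 2.4.4 that the discards outcome is total weighed household discards, with weights by recorded waste type (trim, spoiled, leftovers, plate waste, other) alongside.
- If an avoidable/unavoidable split is reported, derive it by one rule from food description and waste type, fixed before post-course diaries are opened and applied identically to all three waves.
- Report the participant's impression separately, as a perception measure, with its shift across waves.
- Where written descriptions do not separate edible from inedible vegetable trim, show that cell coded both ways.
- Label any numerical illustration as assumed, and show both relabelling directions and several baseline avoidable shares.

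The cost is a few sentences and a lookup table, with no new data collection. The downsides are that total weight includes inedible parts and that the fixed rule is coarse: it holds the definition constant but is not a true measure of avoidability.
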